### Blinding and choice of outcomes

Blinding the treating staff to the intervention is challenging, but the patient will be blinded since all patients will be receiving a standard care variation (routine versus routine plus formalised TTS) and will not be informed of the specific intervention. However, relatively objective endpoints will be adjudicated by a blinded expert panel and a prospective randomised open-label, blinded end-point (PROBE) methodology can be used [24] and has the advantage that procedures resemble real-world practice and are thus more likely to be broadly generalisable [25,26].

## Discussion

### Outcomes and significance

Missed injury in trauma is a common condition in young adults, with potential to lead to prolonged morbidity. The findings of this study may alter the delivery of international trauma care. If formal TTS is (cost-) effective this intervention should be implemented widely, inform guidelines and change practice. If not, where already partly implemented, it should be abandoned. Study findings will be disseminated widely to relevant clinicians and health funders.

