There are a number of potential concerns regarding performing a formalised TTS on every multi-trauma patient. It will take more medical and nursing staff time to perform, and may lead to over-investigation. It could lead to over-diagnosis by labelling minor self-limiting conditions with subsequent patient concern or overconsumption of medical resources. As such, it may feed the notion that even minor, self-limiting injuries should always be diagnosed and actively managed. Additionally, re-examination by the same clinician or team may miss the same injury twice due to systematic error or persistent cognitive error. Ultimately, the decision to implement a formalised TTS procedure relies on the assessment of the clinical effect, as well as the value of the clinical benefits, compared to the associated change in costs. However, in order to provide an evaluation of the cost-effectiveness of a formalised TTS, reliable estimates of the effectiveness of a formal TTS is a necessary requirement.

In summary, questions remain regarding the utility and (cost-) effectiveness of the TTS. Although there is a sound rationale for performing formalised TTS, the current data is inconclusive since the quality of data is low and effect size variable. The health care costs to provide this extra layer of safety-net may not prove cost-effective. This protocol specifies the design for a multicentre clinical trial to assess the effectiveness and feasibility of implementing a formal TSS. The results of the study will provide high level evidence that either a TTS should be mandatory in trauma patients, or that we can save resources if no benefit is found.

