### Aims and hypotheses

Our primary aim is to determine whether the implementation of a formalised TTS will decrease missed injuries post hospital discharge (Type III injuries) and, as secondary aim, increase injury detection in hospital (Type I and II injuries combined). We further hypothesise that the intervention effect will be maintained and that the intervention would lead to decreased clinically significant missed injuries as judged by a blinded expert panel, decreased hospital and ICU bed days, decreased readmissions to hospital, improved quality of life and decreased time off work. We expect complications of the injuries to be the same, but complications of care to be less. If no difference between injury rates is found, we hypothesise that both arms will be equivalent in resource utilisation (ICU and hospital bed days, investigations ordered, interventions required).

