This calculation is consistent with a previous study specifically examining the ICC in trauma receiving hospitals. ICC varied depending on outcome, but the average ICC for blunt trauma the ICC was 0.01 [23]. Assuming an average cluster size of 250 patients, this would mean a total of 3,440 patients would require recruitment (approximately 14 clusters) for the primary hypothesis.

The study is adequately powered for the primary hypothesis, and for several secondary outcomes, such as pre- and post-comparison in Group 2, but not for the pre- and post- comparison in Group 1, measuring maintenance of the intervention effect.

De-identified data will be analysed using SPSS v20.0 software (SPPS Inc, Chicago, IL, USA). For continuous variables, we will use an independent *t*-test and chi-square test will be used to compare differences in proportions. All results will be presented with 95% confidence intervals.

Health economic analyses will include a within trial incremental cost-effectiveness evaluation of formal TTS versus standard care. The outcome measure, incremental cost-effectiveness ratio, directly compares the difference in costs between the formal TTS and standard care with the difference in health related quality of life. Health-related quality of life will be measured in quality adjusted life years (QALYs) derived from changes in EQ-5D-5 L measured at multiple time points. A cost-effective threshold of $AUD 50,000 per QALY will be used to determine whether the intervention was cost-effective and a cost-effectiveness acceptability analysis will be conducted using a range of threshold values from $20,000 to $100,000. A 95% confidence interval around the incremental cost-effectiveness ratio will be estimated using bias-adjusted bootstrapping. In addition, sensitivity analyses and sub-group analyses will be conducted to identify the parameters and patient characteristics that affect the likelihood of the intervention being cost-effective. A *P* value of 0.05 or less will be deemed statistically significant.

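### The stated conclusions allow only adopting or abandoning the formal TTS, although a non-significant primary result could still be compatible with the 5-point reduction the trial is designed to detect

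*Protocol article*

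**What the plan says.** The Discussion (Outcomes and significance) gives two outcomes. The first is "If formal TTS is (cost-) effective this intervention should be implemented widely, inform guidelines and change practice". The second is "If not, where already partly implemented, it should be abandoned". The Discussion paragraph of the abstract carries the same pair. The Background says the results will give high-level evidence that "either a TTS should be mandatory in trauma patients, or that we can save resources if no benefit is found".

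Aims and hypotheses adds a conditional hypothesis: "If no difference between injury rates is found, we hypothesise that both arms will be equivalent in resource utilisation". Bed days, investigations and interventions are named, but no margin is given.

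On analysis, Statistical analysis and sample size states that for continuous variables "we will use an independent *t*-test and chi-square test will be used to compare differences in proportions". It adds "All results will be presented with 95% confidence intervals" and "A *P* value of 0.05 or less will be deemed statistically significant". The same section plans a cost-effectiveness analysis against a threshold of AUD 50,000 per QALY, with a bootstrap interval for the ratio and an acceptability analysis from 20,000 to 100,000. It does not say how an interval for the primary outcome is to be read when the test is not significant.

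**The concern.** A non-significant test of difference can arise in two ways: the effect is absent or too small to matter, or the trial is too imprecise to tell. The interval separates the two. The conclusions as written merge them, because whatever is not shown to be effective falls into the branch that ends in abandonment or saved resources.

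The protocol reasons more carefully elsewhere. In the Background it reports a before-and-after study with similar Type III rates (13.7% and 11.5% at 1 month) and does not read this as no effect, noting that TTS performance may not have risen enough to reveal a difference. The planned trial's own conclusions carry no such caution.

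At stake is the use of an inconclusive trial as grounds for withdrawing a procedure already in use at some hospitals. The article says its findings may alter trauma care internationally.

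**Working it through.** **Inputs** (all from Statistical analysis and sample size):
- Type III rates of 14% and 9%; alpha 0.05; power 0.80; 638 completers per group if individually randomised
- 40% follow-up; 1,595 recruited per cohort for the primary comparison
- 16 hospitals, so 8 per arm under 1:1 allocation
- ICC 0.01, quoted as an average for blunt trauma

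No ICC for Type III injury is given, so 0.005 to 0.02 is used as an assumed range.

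**Step 1. Reproduce the plan's figure.** Two-sided test, pooled variance, no continuity correction:

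n = [1.96 × √(2 × 0.115 × 0.885) + 0.8416 × √(0.14 × 0.86 + 0.09 × 0.91)]² / 0.05² = (0.884 + 0.379)² / 0.0025 ≈ 638 per group.

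638 / 0.40 = 1,595. The figure reproduces exactly, at 80% power with no clustering. Sidedness is not stated; a one-sided test would give 503, so two-sided is inferred.

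**Step 2. Precision with no clustering.** SE = √(0.2023 / 638) = 1.78 points, where 0.2023 = 0.14 × 0.86 + 0.09 × 0.91. Half-width = 1.96 × 1.78 = 3.5 points. An observed reduction between 1.5 points (5 − 3.5) and 3.5 points would be non-significant while its interval still contains 5. The 2.2-point difference in the earlier study (13.7 − 11.5) lies in that band. The problem therefore exists even at the nominal 80% power.

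**Step 3. Precision with clustering.**
- Completers per hospital in 12 months: 638 / 8 = 79.75.
- Design effect: 1 + (79.75 − 1) × 0.01 = 1.79.
- SE = √(0.2023 / 638 × 1.79) = 2.38 points.
- Half-width: 1.96 × 2.38 = 4.7 points, or 2.145 × 2.38 = 5.1 points with t on 14 degrees of freedom (16 hospitals − 2).

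With a half-width of 4.7, any observed reduction from 0.3 to 4.7 points is non-significant and still compatible with 5. If both arms are at 14%, the normal half-width is 1.96 × √(2 × 0.14 × 0.86 / 638 × 1.79) = 5.1 points, so even an observed difference of zero does not exclude 5.

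**Step 4. How often a true 14% to 9% reduction is missed** (valid cluster-adjusted test):

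| ICC | Design effect | Missed, normal | Missed, t (14 df) |
|---|---|---|---|
| 0 (nominal) | 1.00 | 20% | – |
| 0.005 | 1.39 | 34% | 40% |
| 0.01 | 1.79 | 44–45% | 50% |
| 0.02 | 2.58 | 59% | 63% |

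The 44% uses the unpooled SE: power = Φ(5 / 2.38 − 1.96) = Φ(0.14) = 56%. The pooled form gives 55%.

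**Step 5. Other conditions at ICC 0.01.** If all 1,595 per arm had outcome data, 27% would be missed. The chi-square test applied without adjustment would miss about 26%, but its type I error would be 2 × [1 − Φ(1.96 / √1.79)] ≈ 14%, so that lower figure is not a usable one.

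**The case against.** The strongest reply is that the adopt-or-abandon sentences are discussion prose about significance, not a statistical decision rule. Nowhere does the article say that P above 0.05 means no benefit. It promises 95% intervals for every result, and the Background shows its authors can read a null result with care. A reader might infer that non-significance is formally defined as proof of no effect; the document does not say so. What stands is that the article states its conclusions in three places, always as two branches, and none of them mentions the interval.

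A reader might also infer that only tests of difference are planned. That is not so. The intervals and the cost-effectiveness analysis are planned too, and the Discussion sentence turns partly on cost-effectiveness, which does not depend on rejecting a null hypothesis for missed injuries. However, a QALY threshold does not show absence of an effect on Type III injury, the primary outcome, and the Background statement on saving resources is not tied to cost-effectiveness.

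A third tempting reading is that equivalence of resource use is claimed without support. Aims and hypotheses only hypothesises it, and a margin could sit in an analysis plan that is not shown. The missing margin is therefore not itself the finding. The point is that the planned tests of difference cannot support the word.

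Finally, a reader might conclude that the trial would simply miss a real 5-point benefit half the time. That holds only under the stated conditions. The article says the ICC varied by outcome, and the 40% is a 6-month follow-up rate carried forward to 12 months.

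**Conclusion.** The point holds as a fault in the stated conclusions. The abstract, the Background and the Discussion leave no room for an inconclusive primary result, while the design makes one quite possible.

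With 638 completers per arm in 8 hospitals per arm, 40% follow-up, ICC 0.01 and a cluster-adjusted test, the 95% interval extends 4.7 to 5.1 points either side, and a true 14% to 9% reduction is missed 44% to 50% of the time. Over ICC 0.005 to 0.02 the range is 34% to 63%; on the article's individually randomised basis it is 20%. The logical fault does not depend on the ICC, since at ICC 0 there is still a band of non-significant results compatible with the design effect. Clustering widens that band. The article should be corrected on this point, but the planned data collection and analyses are not invalidated by it.

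**What to change.** Restate the conclusions in the abstract, the Background and the Discussion in three parts, based on the cluster-adjusted 95% confidence interval for the difference in Type III injury:

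- **Effective:** the interval lies wholly on the side of benefit.
- **No worthwhile benefit:** the interval excludes a pre-specified smallest worthwhile reduction. That value should be set in advance and be no larger than the 5-point design effect.
- **Inconclusive:** neither of the above applies.

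Report the cost-effectiveness result separately, with its uncertainty, so that it does not stand in for a conclusion about missed injuries. In Aims and hypotheses, replace the statement of equivalence with a difference in resource use reported with its 95% interval, unless an equivalence margin is set in advance.

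The cost is wording only: no change to recruitment, data collection or sample size is needed, and recruitment had not begun at publication. The downside is that the trial may have to report an inconclusive result. This could happen often. At ICC 0.01, if both arms are truly at 14%, the SE is 2.60 points and the half-width 5.09, so the estimate must favour control by 0.09 points before the interval excludes 5. The chance of that is Φ(−0.09 / 2.60), a little under one half.

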## Trial status

Recruitment has not yet begun because we are awaiting funding.

## Abbreviations

AR-DRG: Australian-Revised Diagnostic-Related Group
ATS: Australian Triage Scale
CT: computed tomography
ED: Emergency Department
EDIS: Emergency Department Information System
EMST: Early Management for Severe Trauma
GCS: Glasgow Coma Scale
ICC: intra-cluster correlation
ICU: Intensive Care Unit
ISS: Injury Severity Score
ITT: intention to treat
MRI: magnetic resonance imaging
MBS: Medicare Benefit Scheme
PBS: Pharmaceutical Benefit Scheme
PROBE: prospective randomized, open-label, blinded, end-point
QALY: quality adjusted life year
QoL: quality of life
TTS: trauma tertiary survey
USS: ultrasound scan
